### Quality of life assessment

Participant quality of life will be assessed using both SF-36 questionnaire and fatigue severity scale. A researcher properly familiarized with both tools will perform these assessments.

### Dietary record

Each participant’s food intake in the previous 24 h will be investigated and recorded for later analysis. A nutritionist familiarized with the procedure will perform assessments at all time points. Dietary record data will be analyzed using DietWin 2012 (DietWin Software de Nutrição, Porto Alegre, Rio Grande do Sul, Brazil) professional software.

### Timed up and go test (TUG)

Initially, participants will be positioned sitting on a chair. Then, they will be requested to stand up, walk 3 m, come back, and sit down with no exterior help [29]. Each participant will be timed throughout the trial. These trials will be repeated two times, and the average between trials will be considered for analysis.

### Six-minute walk test (6MWT)

The test will be performed following the American Thoracic Society guideline [30]. In short, participants will be asked to walk back and forth for 6 min along a 30-m corridor marked every 3 m. After 6 min, the total walk distance will be calculated.

### Sitting-rising test (SRT)

The test will be initiated with participants sitting in a chair. Participants will be requested to sit in an upright position with both feet firmly touching the ground and arms crossing their chest. At the researcher signal, the participant will get up and sit down, returning to the initial position. Participants will be encouraged to get up and sit down the maximum number of times in a 30-s period. Only repetitions properly executed will be counted [31].

### Pennation angle (PA)

VL PA will be assessed using B-mode ultrasound at the point corresponding to 50% of the femur’s length. The transducer will be placed longitudinally to muscle tissue and, when necessary, will be laterally tilted to better allow fascicle visualization [32]. Muscle fiber PA will be determined as the intersection of the fascicles with the deep aponeurosis, as assessed with ImageJ angular tool. Each image will be analyzed twice, and the mean value between both analyses will be considered as PA.

### Fascicle length (FL)

B-mode ultrasound will be used for FL assessment at the same site used for PA, with the same probe placement. Linear extrapolation will be used to calculate FL whenever a fascicle extends itself beyond the ultrasound field of view [32]. FL will be calculated two times per image. The mean value will be used as true FL.

## Data analysis

Following visual inspection, data normality will be assessed using the Shapiro-Wilk test. In case of normal distribution, a one-way repeated measures analysis of variance (ANOVA) will be implemented to test for differences in baseline values. Then, a mixed model will be applied for each dependent variable (Child-Pugh class, MELD score, SF-36 and FSS scores, dietary records, TUG, 6MWT, SRT, 1-RM, CSA, PA and FL), having group (BFR-RT and CTRL) and time (0 W, 12 W and 24 W) as fixed factors, and participants as random factors. In case of non-normal data distribution, a Kruskal–Wallis test will be implemented to test for differences in baseline values. Then, the Friedman test will be used to analyze repeated measures. To avoid multiplicity interference on data analysis, adjusted *p* values will be calculated for all variables. Adjusted *p* values will be calculated using Hommel’s procedure, and both adjusted and non-adjusted values will be reported. Additionally, within-group (0-12 W and 0-24 W changes) and between-group effect sizes will be calculated using Cohen’s *d* [33] for each outcome. Finally, the minimal clinically important difference will be analyzed with distribution-based methods [34]. Statistical analysis will be carried out using SAS 9.3 software (SAS institute Inc., Cary, NC).

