### Eligibility criteria

Eligibility criteria are 1) liver cirrhosis diagnosed by histopathological evaluation, hepatic elastography, or by clinic, radiologic or endoscopic criteria and 2) age ≥ 18 and ≤ 70 years. Exclusion criteria are 1) less than 6 months of alcohol abstinence, 2) MELD score > 15, 3) Child-Pugh class C, 4) decompensated chronic diseases, 5) diabetes mellitus, 6) hepatocellular carcinoma or others neoplasia, 7) previous liver transplant, 8) severe ascites, 9) persistent hepatic encephalopathy, 10) coagulation disorders characterized as INR ≥ 1.5 or platelets ≤ 75.000, or 11) medical contraindications for physical exercise practice.

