### Secondary outcomes

#### Child-Pugh class and MELD score

Participant blood samples will be collected and analyzed in a professional clinical laboratory. To classify these samples according to Child-Pugh class and Meld score at 0 W, 12 W and 24 W, they will be screened for aspartate aminotransferase, alanine aminotransferase, creatinine, albumin, and bilirubin. Additionally, clinical screenings will be carried out by a medical professional at the same time points for physical assessment of the participants.

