## Discussion

LC was reported as the 14th most common cause of death worldwide in 2012, resulting in 1.03 million deaths per year [35], with sarcopenia affecting up to 70% of the patients afflicted by LC [3]. If proven efficient in countering sarcopenia onset or reducing sarcopenia progression, new therapeutic options (e.g., BFR-RT) could help reduce the treatment costs of patients with LC.

As such, the present study aims to verify whether BFR-RT will result in important improvements in muscle strength and mass in patients with liver cirrhosis, as well as verifying any significant differences in functional performance and risk of falls. In addition, the LC Child-Pugh class and MELD score will be evaluated in order to determine BFR-RT safety and effects on the disease’s symptoms. To our knowledge, this will be the first intervention study to investigate BFR-RT in this population. Considering that current evidence shows BFR-RT is a safe method, even for frail populations [15, 17, 18], we believe BFR-RT will result in important increases in muscle mass and strength, accompanied by increases in functionality, with no negative outcomes on cirrhosis condition. There are some limitations to this study. The limited follow-up period prevents us from drawing conclusions about the long-term effects of the proposed intervention. Second, we opted to limit our sample to patients without severe LC complications (i.e., Child-Pugh class B and C and MELD > 15), limiting our ability to generalize our results to patients with decompensated LC.

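### Child-Pugh class is analysed as a continuous outcome, so its prescribed route contains no test between arms after baseline

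*Protocol article*

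**What the plan says.** Under Child-Pugh class and MELD score, the purpose of the blood samples is given as "To classify these samples according to Child-Pugh class and Meld score at 0 W, 12 W and 24 W". The Discussion uses class together with MELD to judge whether the training is safe.

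The Data analysis section applies one scheme to every outcome. After visual inspection and a Shapiro-Wilk test, the normal route is that "a mixed model will be applied for each dependent variable (Child-Pugh class, MELD score" and ten further variables), "having group (BFR-RT and CTRL) and time (0 W, 12 W and 24 W) as fixed factors, and participants as random factors". On the non-normal route, baseline values are compared by Kruskal-Wallis, and then "the Friedman test will be used to analyze repeated measures". Cohen's d, within and between groups, is calculated for each outcome on either route. No method for categorical or ordinal data is named.

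On the levels that class can take at entry, the Eligibility criteria exclude "3) Child-Pugh class C" and do not mention class B. The Discussion describes the sample as "patients without severe LC complications (i.e., Child-Pugh class B and C and MELD > 15", which reads as if class B were excluded too.

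**The concern.** Shapiro-Wilk asks whether data could come from a continuous normal distribution. A variable with two or three possible values cannot look normal in a sample of this size, so the outcome of the check is settled before any data arrive. The variable is then sent to Friedman, which ranks visits within participants and has no place for treatment group.

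The trial is randomised with a sham control so that change under training can be set against change without it. For class, one of the two disease-severity measures that the Discussion ties to safety, the prescribed tests do not make that comparison after baseline.

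**Working it through.** The plan gives no figure on this point to reproduce. The target of 30 comes from the Design overview. Two inputs are assumed because the article does not state them: 15 per arm and a two-sided alpha of 0.05.

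**Step 1: can class pass the normality check?** Shapiro-Wilk was computed for every possible non-constant split of participants over class codes. The table gives the split most favourable to normality.

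| Levels present | n | Largest p |
|---|---|---|
| Two | 15 | 0.000066 (W = 0.643) |
| Two | 30 | 0.00000022 (W = 0.638) |
| Three (some reach class C) | 15 | 0.0073 (split 4/7/4) |
| Three | 30 | 0.00011 (split 8/14/8) |

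Every value is below 0.01, so the result is the same for any alpha from 0.01 to 0.10. If all participants are class A at 0 W, the baseline values are constant and the test is undefined for them.

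**Step 2: what does Friedman then report?** Constructed data: 15 per arm, 7/15 in class B at 0 W in each arm, and 12 W values carried to 24 W. Participants who do not change class get ranks 2, 2, 2. Those who worsen get 1, 2.5, 2.5. Those who improve get 3, 1.5, 1.5.

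*One arm, 5 of 15 worsen.*
- The rank sums are 25, 32.5 and 32.5, around an expected 30. The squared deviations total 25 + 6.25 + 6.25 = 37.5.
- The uncorrected statistic is 12/(15 × 3 × 4) × 37.5 = 2.5.
- The tie correction is 1 − (5 × 6 + 10 × 24)/(15 × 3 × 8) = 1 − 270/360 = 0.25.
- Chi-square is 2.5/0.25 = 10 on 2 df, so p = exp(−5) = 0.007.

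*Opposite effects: 5/15 worsen in one arm and 5/15 improve in the other.*
- Class B at 12 W is 7 + 5 = 12 of 15 versus 7 − 5 = 2 of 15. Fisher's exact test gives p = 0.0007.
- In the pooled Friedman test the rank deviations cancel: chi-square 0, p = 1.0.

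*Identical arms: 5/15 worsen in both.*
- Pooled chi-square is 20, so p = exp(−10) = 0.00005.

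Pooled Friedman therefore misses a large difference between arms and is significant when there is none. Run separately in each arm, it gives p = 0.007 in both arms under both scenarios, so it does not tell worsening from improvement either.

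**Step 3: what could a valid comparison deliver?** For Fisher's exact test on worsening by at least one class, with none in the other arm:
- 4/15 versus 0/15: p = 2 × C(15,4)/C(30,4) = 2 × 1,365/27,405 = 0.10.
- 5/15 versus 0/15: p = 2 × C(15,5)/C(30,5) = 2 × 3,003/142,506 = 0.042.

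Five events against none is thus the smallest significant result of this kind. Exact power against an assumed 5% worsening in the other arm is 8%, 27%, 52% and 74% for assumed rates of 20%, 30%, 40% and 50%. An arm with 0/15 worsening still has an exact 95% upper limit of 1 − 0.025^(1/15) = 21.8%.

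**The case against.** Several stronger readings are tempting, and the article does not support them.

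- *The arms are never compared on class.* Too strong. Kruskal-Wallis compares them at baseline, and a between-group Cohen's d is prescribed for each outcome. What is missing is a test after baseline. The d does not fill the gap, because its value depends on the numbers given to A, B and C.
- *Failure of the normality check is certain however it is done.* It is certain for raw class codes, the natural reading of a check on data normality. In simulations at n = 30, with an assumed 20–50% in class B and 10–40% switching class, change scores were rejected in every run, but approximate mixed-model residuals in about 74–100%.
- *Cohen's d would divide by zero.* This needs a baseline standard deviation as the divisor, and the article names no divisor. It also needs the Discussion's wording on class B to override the Eligibility criteria.
- *Safety could not be judged, or deterioration would go unseen.* MELD is assessed, adverse events are a stated aim, and clinical screening takes place at all three visits.
- *The numeric Child-Pugh score is already on file.* The article never mentions one.

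Two further objections stand in part. The missing group term in Friedman affects every outcome that fails the check, so class is one instance of a wider weakness. It is, however, the instance where failure is built in, and it needs a categorical or ordinal method whatever replaces Friedman. A valid test will also be weak with 30 participants. That is a reason to rely on counts and intervals, not to keep a test that does not address the comparison.

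**Conclusion.** The concern holds in limited form. With raw class codes that vary, at n = 15 to 30, the scheme always leads to Kruskal-Wallis at baseline and Friedman over time. There is then no test between arms after baseline, and the only between-arm summary is a Cohen's d on arbitrary codes. The safety evaluation is weakened but not removed.

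The size of the problem is shown by Friedman p = 1.0 for 12/15 versus 2/15 and p = 0.00005 for identical arms. Those figures come from constructed data with an assumed 15 per arm; they illustrate the defect and do not forecast the trial's results. The conclusion does not depend on which statement about class B is right, but that contradiction needs settling because it determines which shifts are possible.

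**What to change.** 1. Remove Child-Pugh class from the list of outcomes subject to the normality check, the mixed model and Cohen's d.
2. Report shifts in class from 0 W to 12 W and from 0 W to 24 W as counts per arm, with exact 95% intervals for the proportion that worsens.
3. Compare worsening between arms with an exact test or an ordinal model, and state that precision is low with 30 participants, so that a non-significant result is not read as evidence of safety.
4. If the numeric Child-Pugh score is recorded, which is an assumption, it may be analysed between arms at 12 W and 24 W adjusted for its 0 W value.
5. Reconcile the Eligibility criteria and the Discussion on whether class B is eligible.

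Items 1 to 3 change analysis wording only: class is already determined at all three visits, and no extra participants or visits are needed. The Trial status section says that recruitment was still ongoing at submission, and the article reports no data analysed, so on that account the change could be fixed in advance. The cost of item 4 cannot be judged from the article.

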**Methods:**

Thirty participants will be randomly distributed between 1) BFR-RT and 2) control (CTRL). Assessments will occur at three time points: before the training intervention (0 W), after 12 weeks (12 W), and at follow-up (24 W). The following variables will be assessed: Child-Pugh classification; MELD score; SF-36 questionnaire; fatigue severity index; 6-min walk test; timed-up and go; 30-s sitting and rising test; dietary record; one-repetition maximum (1-RM) strength test (knee extension exercise); and vastus lateralis’ cross-sectional area, Pennation angle, and fascicle length. The BFR-RT group will undergo 12 weeks of knee extension exercise (1 × 30 repetitions and 3 × 15 repetitions at 20% 1-RM and 50% of total blood flow occlusion pressure), with two sessions per week. Data normality will be assessed using the Shapiro-Wilk test. In case of normal distribution, a one-way repeated measures analysis of variance will be implemented to test for differences in baseline values. A mixed model then will be applied for each dependent variable. In case of non-normal data distribution, a Kruskal–Wallis test will be implemented to test for differences in baseline values. Next, the Friedman test will be used to analyze repeated measures. Within- and between-group effect sizes will be calculated using Cohen’s *d* for each outcome. Finally, the minimal clinically important difference will be analyzed with distribution-based methods.

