### Randomization

Initially, all participants will be pooled into a single group. This group then will be organized into quartiles according to participants’ initial 1-RM and vastus lateralis CSA. Next, participants in each quartile will be allocated to either the training (BFR-RT) or control group (CTRL) using a maximally tolerated imbalance model [22]. An unpaired T test will be applied to ensure no baseline difference between groups. If significant between-groups differences are detected, the randomization procedure will be repeated until a random distribution with no significant difference is achieved. The Berger-Exner test will be performed during data analysis to verify for selection bias [23].

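### Allocation is stratified by quartiles of baseline 1-RM and VL CSA but the mixed model omits the stratum: the group test as written is too conservative for the two primary outcomes, while a group-by-time contrast loses little

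*Protocol article*

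**What the plan says.** **Allocation (Protocol article, Randomization).** All participants are first pooled. "This group then will be organized into quartiles according to participants’ initial 1-RM and vastus lateralis CSA". Then "participants in each quartile will be allocated to either the training (BFR-RT) or control group (CTRL) using a maximally tolerated imbalance model". If a baseline t test is significant, "the randomization procedure will be repeated until a random distribution with no significant difference is achieved". The section does not say how the two variables form one set of quartiles, and it gives no imbalance limit.

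**Primary outcomes (Assessments).** These are 1-RM and VL CSA, so the stratifying variables are the baseline values of the primary outcomes.

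**Model (Data analysis).** If data are normal, "a mixed model will be applied for each dependent variable", "having group (BFR-RT and CTRL) and time (0 W, 12 W and 24 W) as fixed factors, and participants as random factors". No quartile, baseline 1-RM or baseline CSA term is listed, and no group-by-time term is written. The same section asks for effect sizes on 0-12 W and 0-24 W changes.

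**The concern.** Balancing arms within strata that predict the outcome reduces the true sampling variance of the arm difference. A model that ignores the strata leaves the between-stratum spread in the participant variance, so its standard error does not reflect that gain. Intervals are then too wide and p values too large. The repeated randomisation works in the same direction, because it also removes allocations with large baseline differences.

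At stake is power. The target is 30 participants, about 15 per arm if allocation is equal. The design builds in balance on 1-RM and CSA, and the stated analysis may fail to use it.

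**Working it through.** **Inputs.** From the article: n = 30, two arms, allocation within quartiles, visits at 0, 12 and 24 W, and the model terms above. Assumed, because the article does not give them: 15 per arm, outcome SD 1, equal correlation rho between visits, quartiles of a combined 1-RM and CSA score (four levels), imbalance limit 1 or 2, two-sided 5% without the Hommel adjustment, complete data. The article gives no power calculation to reproduce.

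**Step 1. What the unstratified model reports.** With complete data the group test compares participant means over three visits.

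- Variance of a participant mean: (1 + 2 rho)/3.
- Model SE: sqrt[(2/15)(1 + 2 rho)/3], which is 0.298 at rho 0.5, 0.313 at 0.6, 0.340 at 0.8 and 0.353 at 0.9.

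For a 0 to 12 W change, the variance is 2(1 - rho) and the SE is sqrt[(2/15) × 2(1 - rho)], which is 0.365, 0.327, 0.231 and 0.163 at the same four values.

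**Step 2. Why the two contrasts differ.** The share of variance explained by the outcome's own baseline value is (1 + 2 rho)/3 for the participant mean: 0.67 at rho 0.5 and 0.87 at 0.8. For the change it is (1 - rho)/2: 0.25 at rho 0.5 and 0.10 at 0.8. Strata built on baseline therefore matter greatly for the group effect and little for change, and less as rho rises.

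**Step 3. Simulated group effect on 1-RM, no true effect** (3,000 trials per setting, limit 2, randomisation repeated until both baseline t tests exceed 0.05; ratios from unrounded values).

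| rho | Model SE, no stratum | True SD | Ratio | False positives, no stratum | False positives, with stratum |
|---|---|---|---|---|---|
| 0.6 | 0.312 | 0.247 | 1.26 | 1.4% | 5.8% |
| 0.8 | 0.342 | 0.251 | 1.36 | 0.4% | 4.7% |
| 0.9 | 0.354 | 0.247 | 1.44 | 0.3% | 5.1% |

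The model SEs match Step 1. With the stratum, the model SE is 0.221, 0.219 and 0.214, against a true SD of 0.229, 0.220 and 0.221. The 0.3% is within simulation error of 0.4%: sqrt(0.004 × 0.996/3000) is about 0.1 percentage points. A simulation with limit 1 and no repeated randomisation gave 0.30 against 0.23 at rho 0.5 and 0.34 against 0.24 at rho 0.8, with false-positive rates of 0.4% to 1.4%.

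**Step 4. Power of the group effect.**

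- Effect of 0.8 SD at 12 W and 24 W, limit 1, without and with stratum: 38% and 62% (rho 0.5), 29% and 59% (0.7), 26% and 60% (0.8).
- Same effect, limit 2 with repeated randomisation: 23% to 37% without, 59% to 62% with.
- Effect of 0.5 SD at 12 W and 0.25 SD at 24 W, limit 2 with repeated randomisation: 5.8% and 19.1% (rho 0.6), 3.8% and 18.7% (0.8), 4.0% and 20.5% (0.9).

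**Step 5. Group-by-time contrast, 0 to 12 W.** Under no effect the model SE is 0% to 6% too wide. Power without and with stratum-by-time:

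- 0.8 SD effect: 58% and 62% at rho 0.5.
- 0.5 SD effect: 30.8% and 33.5% at rho 0.6, 57.0% and 57.6% at 0.8, 85.8% and 85.6% at 0.9.

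A stratum main effect does nothing here. In one simulated data set fitted as a mixed model, the contrast SE was 0.259 with and without it, and 0.250 with stratum-by-time. The group SE without interaction fell from 0.386 to 0.231.

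**Step 6. A secondary outcome correlated 0.3 with strength.** The ratio of model SE to true SD for the unstratified model is 0.98 to 1.04. Adding the stratum changes power for the group effect by 1 point or less.

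**The case against.** The strongest objection is that the large figures belong to a contrast nobody would choose. Because 0 W is a level of time, the group main effect averages a pre-treatment visit with two later ones: a 0.8 SD effect at 12 W and 24 W is diluted to (0 + 0.8 + 0.8)/3 = 0.53 SD. The Aims concern the effects of training and their retention, and the effect sizes are for change. For a 0.8 SD effect, the 0 to 12 W contrast without any stratum has power of 58%, 79% and 93% at rho 0.5, 0.7 and 0.8. The group effect with the stratum has 62%, 59% and 60%. From rho 0.7 upward, choosing the right contrast matters more than adding the stratum.

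This stands and limits the size of the point. It does not remove it, because the article names the model's factors and that list does not match the allocation.

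It can also be said that an article condenses a fuller plan, where stratification terms often sit. That is fair for silence, but here the factors are stated.

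Two further objections stand. The direction is conservative, so no false claim of benefit follows. And the article does not say how 1-RM and CSA are combined: crossed quartiles would give up to 4 × 4 = 16 cells for 30 people.

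**Conclusion.** The model as written ignores the stratified allocation. For the group effect on 1-RM, the standard error is roughly 25% to 45% too wide at correlations of 0.5 to 0.9, and the false-positive rate is about 0.4% to 1.4% instead of 5%. CSA, as the other stratifier, should behave alike. If a group-by-time contrast is the intended test, the loss is about 4 power points at correlation 0.5 and about 1 or less from 0.7 upward. These sizes depend on the assumed correlations, effect sizes, imbalance limit and four-level composite quartile.

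A reader might infer three stronger things that the article does not support:

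- **That type I error is inflated.** The error runs the other way.
- **That the trial's main comparison must lose a large share of its power.** That holds only if the averaged group effect is the test, and the aims point elsewhere.
- **That every outcome is affected.** Where an outcome correlates weakly with strength or muscle size, the effect is near zero.

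**What to change.** In Data analysis, add the allocation stratum defined under Randomization to the mixed model for 1-RM and CSA:

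- as a main effect, where the group effect is tested;
- as stratum plus stratum-by-time, where a between-arm contrast at a visit or in change is reported, because a main effect alone leaves a within-participant contrast unchanged.

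State which contrast is the test, and say under Randomization how 1-RM and CSA form the quartiles, so that the term is defined.

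The cost is a line or two of model wording, with no extra patients, visits or measurements. With four composite quartiles it uses three degrees of freedom, or 3 + 6 = 9 with stratum-by-time; crossed quartiles would use more. The quartiles have to exist before allocation, so the stratum should be available for each participant, although the article does not say that it is kept in the data set. Extending the term to the other outcomes is optional.

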**Fig. 2 Fig2:**
[figure not shown]
Design overview. Before the training period (0 W), all participants will be screened for Child-Pugh class and MELD score, as well as for quality of life, functional capacity, and risk of falls Participants will also be requested to provide a dietary record for caloric intake calculation. At least 48 h later, participants will perform a 1-RM test. Then 72 h later, vastus lateralis muscle CSA, PA, and FL will be assessed. Participants will then be randomly allocated between a training (resistance training with blood-flow restriction - BFR-RT) and control (CTRL) group. After 12 weeks of intervention (12 W), all of the previous parameters will be reassessed. A no-intervention period of 12 weeks will be carried out and, at follow-up (24 W), participants will be reassessed in order to verify the interventions carryover effects

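### The mixed model states no group-by-time term, baseline adjustment or between-group contrast at 12 W or 24 W, so no stated test targets the training effect or its retention.

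*Protocol article*

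**What the plan says.** The Data analysis section applies one mixed model to every dependent variable, "having group (BFR-RT and CTRL) and time" (0 W, 12 W, 24 W) "as fixed factors, and participants as random factors". Neither that section nor the abstract's Methods mentions a group-by-time interaction, a baseline covariate or a named contrast.

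Three other places bear on how this model behaves:

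- **0 W precedes allocation.** The Fig. 2 caption places the baseline assessments first and then says "Participants will then be randomly allocated between a training (resistance training with blood-flow restriction - BFR-RT) and control (CTRL) group".
- **0 W is pushed towards balance.** Under Randomization, participants are grouped into quartiles by initial 1-RM and vastus lateralis CSA. If a t test finds a baseline difference, "the randomization procedure will be repeated until a random distribution with no significant difference is achieved".
- **There are two separate questions.** The Aims list the effect of BFR-RT on strength and muscle, and separately its retention 12 weeks after training ends. 1-RM and CSA are the primary outcomes.

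Change from baseline appears only in the effect sizes: within-group Cohen's d for 0-12 W and 0-24 W, beside a between-group d. No test is tied to these.

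**The concern.** In a randomized design measured at 0, 12 and 24 W, the training effect is the between-group difference at 12 W given baseline, or equivalently the difference in change. Retention is the same quantity at 24 W. A model with only additive group and time terms contains neither. Its group coefficient mixes a visit where the true difference is zero, the visit just after training, and a visit after 12 weeks without training.

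With 30 participants the trial has little power to spare. A diluted estimate would understate the effect on 1-RM and CSA and make a null result hard to interpret. If the interaction is intended but unstated, the choice between group effect, omnibus interaction and pairwise comparisons stays open until the data are seen.

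**Working it through.** The document gives no power, alpha, effect size, SD or correlation, so there is no stated figure to reproduce.

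**Inputs.** From the article: 30 participants, two groups, visits at 0, 12 and 24 W. Assumed: 15 per arm (the ratio is not stated), two-sided alpha 0.05, no dropout, unit SD. Let d be the group difference at 12 W in SD, r the share of d still present at 24 W, and ρ the within-person correlation.

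**1. What the additive group coefficient estimates.** With balanced data it is the mean of the three group differences: (0 + d + r·d)/3 = d(1 + r)/3.

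| Retention r | Share of d kept |
|---|---|
| 0 | 1/3 = 33% |
| 0.5 | 1.5/3 = 50% |
| 1 | 2/3 = 67% |

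This depends only on r and on balance.

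**2. Power of that test against a 0-12 W contrast, common ρ.** The variance of the averaged effect is (2/n)(1 + 2ρ)/3. That of the difference in 0-12 W change is (2/n)·2(1 − ρ). Using the noncentral t with 28 df, n = 15 and d = 0.8:

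| ρ | Group effect, r = 0 to 1 | 0-12 W change |
|---|---|---|
| 0.5 | 14-41% | 56% |
| 0.7 | 12-35% | 78% |
| 0.9 | 11-31% | 99.7% |

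Fitting both mixed models to simulated data (300 runs per setting, ρ = 0.7, d = 0.8) gave group coefficients of 0.26, 0.41 and 0.53 for r = 0, 0.5 and 1. The 12 W interaction coefficient was about 0.80 each time.

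**3. If the interaction is included.** Simulation with effects of 0.8 SD at 12 W and 0.4 SD at 24 W and simple allocation:

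| Correlations 0-12 / 0-24 / 12-24 | Group effect | 2-df interaction | 12 W change | 12 W ANCOVA |
|---|---|---|---|---|
| 0.8 / 0.7 / 0.8 | 21-22% | 83% | 92% | 93-94% |
| 0.6 / 0.5 / 0.6 | 24% | 52-54% | 64-65% | 72-74% |

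A hand check on ANCOVA: its residual SD is √(1 − ρ²), so √(1 − 0.64) = 0.6 and √(1 − 0.36) = 0.8. The noncentralities are 0.8/(0.6·√(2/15)) = 3.65 and 0.8/(0.8·√(2/15)) = 2.74, in line with the table.

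The gap depends on retention. With common ρ = 0.7 and d = 0.8, the omnibus test has 69% power at r = 0.5 and 82% at r = 0 or 1, against 84% for ANCOVA. At ρ = 0.9, d = 0.5 and r = 0 or 1 it is slightly ahead (88% against 86%), but it still does not say at which visit the groups differ.

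**4. Random intercept and the 0-24 W contrast (secondary).** A participant intercept alone implies one common correlation. Assume correlations of 0.8 (0-12), 0.9 (12-24) and 0.6 (0-24), with mean 0.767. The model then uses a difference variance of 2(1 − 0.767) = 0.467, where the true 0-24 W value is 2(1 − 0.6) = 0.80. The ratio is 1.71, and simulated type I error is 13-14%. With 0.8, 0.8 and 0.7 the true value is 0.60, the ratio 1.29, and the error about 8%. For 0-12 W the true value is 2(1 − 0.8) = 0.40, below 0.467, so that contrast is slightly conservative.

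**The case against.** The strongest reply is that the section lists factors, not model terms. Naming group and time is common shorthand for a crossed model. The text neither excludes the interaction nor calls the group main effect the test, and the change-based effect sizes show that change is of interest. This stands. A reader might infer that the trial will certainly test the averaged group effect, and the document does not support that.

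A reader might also infer that the model misses most of the 12-week effect. That holds only if less than half is retained at 24 W, and retention is unknown because it is itself an aim.

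A third tempting reading is a collapse in power from about 94% to 9%, with type I error near 0.1%. Those figures arise when allocation is simulated as tightly stratified on the outcome's own baseline. They also assume the correlations, the effect and 50% retention. The article does not say how the 1-RM and CSA quartiles combine, and its allocation method tolerates some imbalance. The figures also cannot be carried over to outcomes that play no part in allocation.

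Finally, covariance structure and degrees-of-freedom method are commonly left to an analysis plan. That is fair, and the covariance point is offered only as a suggestion. The reply does not remove the core point. The article does fix the model's factors and names no contrast, and supplying the interaction still leaves an omnibus test that addresses neither aim directly.

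**Conclusion.** The point holds as a defect of specification. As stated, the model contains no parameter for the 12 W training effect or for 24 W retention. On the literal reading the group coefficient keeps 33% to 67% of the 12 W effect. That result needs only balanced data and a zero true difference at 0 W.

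On the charitable reading, the omnibus interaction loses about 10 to 20 points of power against a baseline-adjusted 12 W contrast. That rests on 15 per arm, effects of 0.8 SD and 0.4 SD, and the assumed correlations. The gap narrows, and can slightly reverse, when retention is nil or complete. The 8-14% type I error for the 0-24 W contrast applies only if correlation decays over time in the way assumed. The article fixes no primary time point, so taking 12 W, the end of training, as primary is a recommendation.

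**What to change.** Replace the model sentence so that it does the following:

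- Includes group-by-time and adjusts for the outcome's own 0 W value and for baseline 1-RM and CSA, which form the allocation quartiles. A constrained longitudinal model with a common 0 W mean is an acceptable alternative.
- Names BFR-RT minus CTRL at 12 W as the primary contrast for 1-RM and CSA.
- Names the same difference at 24 W, with its 95% CI, as the retention contrast.
- As a secondary suggestion, uses an unstructured within-participant covariance instead of a random intercept alone.

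The cost is one or two model degrees of freedom and a few lines of code. No extra data are needed, since all of these measurements are already scheduled. The article reports recruitment as ongoing at submission, so the wording could be fixed before analysis.
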